**Sites:** 7 hospitals, 4 in western Kenya and 3 in Uganda, in areas with moderate to intense malaria transmission. The number of hospitals will be expanded if recruitment if so required.

**Study Population:** Inclusion criteria: convalescent children aged less than 5 years and weighing  $\geq 5$  kg admitted with severe anaemia (haemoglobin  $< 5$ g/dL / Ht  $< 15\%$ ); clinically stable, able to take or switch to oral medication; post-transfusion Hb  $> 5$ g/dL. Exclusion criteria: blood loss due to trauma, malignancy, known bleeding disorders or sickle cell disease, known hypersensitivity to study drug, known heart conditions, non-resident in study area, previous participation in study, known need at enrolment for prohibited medication and scheduled surgery during the 6-month course of the study. HIV infection and cotrimoxazole prophylaxis are not exclusion criteria.

**Study Interventions:** Children in both arms will receive standard in-hospital care for severe anaemia (blood transfusion, often combined with quinine or artesunate IV/IM). All children will then receive a 3-day course of AL (whether they initially had malaria or not), which will be started in-hospital as soon as they are able to take oral medication, and will be completed at home after discharge. At 2 weeks after enrolment surviving children will be randomized to receive either a standard 3-day

courses of DP (Eurartesim®, Sigma Tau, Italy) or an identical placebo regimen at 2, 6 and 10 weeks after enrolment.

**Outcome Measures:** Primary: Death or all-cause re-admission by 6 months from randomization (composite primary outcome). Key secondary: 1) all-cause mortality, 2) all-cause hospital readmission, 3) readmissions due to severe anaemia or severe malaria (requiring parenteral quinine or artesunate), 4) non-severe all-cause sick-child clinic visits, 5) clinic visit because of RDT or microscopy confirmed non-severe malaria.

**Follow-up procedures:** Children will be followed for 6 months by passive case detection in 3 phases: Pre-PMC (2 weeks between discharge and randomisation); PMC (2-14 weeks post-discharge); post-PMC (extended follow period from 15 to 26 weeks post-discharge).

**Sample size:** A sample size of 520 children per arm (1040 total children) allows detection of a 25% reduction in the incidence rate from 1,152 per 1000 child years (530 per 1000 children per 24 weeks) to 864 per 1000 child years, with 10% loss to follow-up (power 80%,  $\alpha=0.05$ ).

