| Treatment for severe malaria                                                                                                                                   | Parenteral artesunate / quinine and oral AL, 3 days |                                    | Parenteral artesunate / quinine and AL |

An end of study assessment will be done 26 weeks (6 months) after discharge.  
 AL=artemether-lumefantrine. PMC=Post-discharge Malaria Chemoprevention. DP=dihydroartemisinin-piperaquine.  
 QN=quinine

Table 2: Study Design and Schedule of Assessment

| Phase                                      | Recruitment Phase       | Enrolment                            | In-patient Hospitalisation phase |                       |                       | Randomisation                                                                     | PMC
Treatment Phase
12 weeks period from 2-14 weeks |       |                                                                                    |       |       |                                                                                        |       |       |                                          | Post-PMC
Extended follow-up Phase |
|--------------------------------------------|-------------------------|--------------------------------------|----------------------------------|-----------------------|-----------------------|-----------------------------------------------------------------------------------|-----------------------------------------------------------|-------|------------------------------------------------------------------------------------|-------|-------|----------------------------------------------------------------------------------------|-------|-------|------------------------------------------|--------------------------------------|
| Location                                   | In-Hospital             |                                      |                                  |                       |                       | Clinic/
Home                                                                   | Home                                                      |       |                                                                                    |       |       |                                                                                        |       |       |                                          | Clinic/home                          |

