| Visit number                               | #1                      | #2                                   | #3                               |                       |                       | #4                                                                                |                                                           |       | #5                                                                                 |       |       | #6                                                                                     |       |       | #7                                       |                                      |
| Visit description                          | Pre-study Screening     | Screening
Consent & Base-
line | AL treatment visit               |                       |                       | t=2 weeks;
Allocation &
treatment visit                                     |                                                           |       | t=6 weeks
treatment visit                                                       |       |       | T=10 weeks
treatment visit                                                          |       |       | End of study
Assessment               |                                      |
| Study Time                                 | Days -4 a -0 | Day0                                 | Day0
Hosp                     | Day1
hosp/
home | Day2
hosp/
home | 2 weeks (day 14[11-28]) c
2w-
Day1    2w-
Day2    2w-
Day3 |                                                           |       | 6 weeks (day 42 [38-56]) c
6w-
Day1    6w-
Day2    6w-
Day3 |       |       | 10 weeks (day 70 [66-84]) c
10w-
Day1    10w-
Day2    10w-
Day3 |       |       | 6 Month
(day 182 +/- 28) c |                                      |

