#### 8.4.3.2. Exclusion criteria for randomisation:

1. Used DP since enrolment
  2. Use or known need at the time of randomisation for concomitant prohibited medication (see section 8.5.7.2, page 35) during the 14 weeks PMC treatment period (see section 8.5.7.2, page 35).
  3. Enrolled, or known agreement to enrol into another clinical trial involving ongoing or scheduled treatment with medicinal products during the course of the study (6 months from enrolment)
  4. A known need at the time of randomisation for scheduled surgery during the subsequent course of the study (6 months from enrolment)
  5. Suspected non-compliance with the follow-up schedule
  6. Withdrawal of consent since enrolment
- Readmission or re-transfusion in the 2 week period since enrolment or on the day of randomisation screening is not an exclusion criteria for randomization but require a delay of randomisation so that a minimum of 12 days and a maximum of 21 days have passed since the most recent discharge if artemether-lumefantrine was provided around the time of (re)discharge, provided the patient has clinically recovered and is stable and fulfils the randomisation eligibility criteria on the re-scheduled day of randomisation.

---

 See Section 8.5.7.2 “Concomitant and prohibited Medications”, page 34

- Fever ( $\geq 37.5^{\circ}\text{C}$ ) on the day of randomisation screening is not an exclusion criteria for randomization but requires a delay of randomisation. Febrile children will be screened for malaria using RDTs or malaria smears, and RDT or smear positive children will be treated with a repeat course artemether-lumefantrine. They will be eligible for randomisation when a minimum of 12 days and a maximum of 21 days have passed since the first day of the repeat course of artemether-lumefantrine, provided the patient has clinically recovered and is stable and fulfils the randomisation eligibility criteria on the re-scheduled day of randomisation.

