## 8.5.2. Trial Medication and Interventions

### 8.5.2.1. PMC intervention schedule

Children will be randomised to one of the 2 treatment groups: Children in both arms will receive standard in-hospital care for severe (malarial) anaemia (blood transfusion, with or without antimalarial treatment with artesunate IV/IM). They will then all receive a 3-day course of artemether-lumefantrine (Coartem®, Novartis Pharmaceuticals) (AL) regardless of whether they were admitted with severe malarial anaemia or severe anaemia without evidence of malaria. At 2 weeks post-discharge, surviving children will be randomized to receive a standard 3-day course of DP at 2, 6, and 10 weeks post-discharge or an identical placebo regimen (Table 1, page 14). If children receive AL for malaria during any unscheduled out-patient visit or during a readmissions, the PMC schedule will be adapted accordingly such that any next course of DP is given at least 2 weeks after the start of the last course of AL; e.g. if a child was due to receive the 2nd course of DP at 6 weeks post-discharge, but is treated for malaria with AL during an unscheduled visit at 5 weeks, then the 6-week course of DP (or placebo) is provided in week 7 instead of week 6, and the subsequent course in week 11 instead of week 10.

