#### **8.5.7.1. Permitted Medications during follow up period**

During the treatment and follow-up phase of the study if a subject is diagnosed with malaria the investigator will prescribe antimalarial treatment based on the severity of the malaria illness as indicated in Table 1: Study treatment and phases, page 14.

Use of cotrimoxazole (which has some antimalarial properties) treatment or prophylaxis is not considered prohibited as short-courses are commonly prescribed for the treatment of bacterial infection. Daily cotrimoxazole prophylaxis is used by HIV-infected and exposed children.

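### Non-severe malaria before randomisation: Table 1 and section 8.4.3.2 name different drugs, and the wait before the first DP/placebo course is defined only after AL

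*Protocol*

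**What the plan says.** Table 1 (Protocol, 3.2) sets treatment by period. For acute malaria, the Pre-PMC column gives oral quinine for 7 days, and the PMC and Post-PMC columns give AL for 3 days. Severe malaria has its own row, which for the Pre-PMC period reads "Parenteral artesunate / quinine and oral AL, 3 days". The same section describes the first follow-up phase as "Pre-PMC (2 weeks between discharge and randomisation". Section 8.5.7.1 sends the reader to that table: "the investigator will prescribe antimalarial treatment based on the severity of the malaria illness as indicated in Table 1".

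Section 8.4.3.2 deals with fever on the day of randomisation screening. It delays randomisation, calls for a malaria test, and states that "RDT or smear positive children will be treated with a repeat course artemether-lumefantrine". Randomisation may follow once "a minimum of 12 days and a maximum of 21 days have passed since the first day of the repeat course of artemether-lumefantrine". For a child readmitted or re-transfused since enrolment, the same 12 to 21 days are counted "since the most recent discharge if artemether-lumefantrine was provided around the time of (re)discharge".

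Section 8.5.2.1 spaces study courses after malaria treatment: "any next course of DP is given at least 2 weeks after the start of the last course of AL". Table 2 places the randomisation visit at "2 weeks (day 14[11-28" days after enrolment.

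**The concern.** Two instructions appear to apply to one child. A febrile, test-positive child at the screening visit is not yet randomised. On the summary's definition that child is still in the Pre-PMC phase, where Table 1 gives quinine, while 8.4.3.2 gives AL. Nothing in the protocol says which prevails.

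The second problem does not depend on the first. Passive surveillance starts at enrolment, so visits for malaria in the first 2 weeks are foreseen, and Table 1 is the only passage that says how to treat non-severe malaria found then. It gives quinine, yet no passage gives an interval between quinine and the first DP/placebo course.

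At stake are consistency between sites in treatment, timing of randomisation and drug background at the first study course, and the safety of starting DP close to another antimalarial.

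**Working it through.** No power, alpha or event figure enters this point. The check is a comparison of passages plus day counts.

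**Step 1. Which column of Table 1 applies at the screening visit?**

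- *By phase.* The summary ends Pre-PMC at randomisation. A child at the screening visit is not randomised, so the column gives quinine. Section 8.4.3.2 gives AL. Conflict at every such visit.
- *By calendar.* Table 1's axis is weeks since enrolment, and the PMC period is weeks 2 to 14. From day 14 the column gives AL, in line with 8.4.3.2. The visit window opens on day 11, so the conflict remains for days 11, 12 and 13.

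Both readings concern non-severe malaria only. The severe row ends in AL and fits the readmission rule.

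**Step 2. What the delay rule gives after AL.** Earliest day = visit day + 12; latest day = visit day + 21, with AL started at the visit.

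- Visit on day 14: 14 + 12 = 26 to 14 + 21 = 35.
- Visit on day 11: 11 + 12 = 23 to 11 + 21 = 32.

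Both upper limits pass day 28, where the Table 2 window closes. After quinine given at the screening visit, neither limit can be derived from the text.

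**Step 3. A child given quinine at an earlier unscheduled visit.** A 7-day course begun on day s has its last day on s + 6.

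- s = 8: last day 8 + 6 = 14, the scheduled randomisation day.
- s = 13: last day 13 + 6 = 19, which is 5 days after it.
- s = 7: last day 7 + 6 = 13, the day before it.

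If this child is afebrile, clinically stable and was not readmitted or re-transfused, neither delay provision in 8.4.3.2 is triggered, and the visit may take place anywhere in the window. For s = 8, a visit on day 11 falls on quinine day 11 − 8 + 1 = 4. A visit on day 28 falls 28 − 14 = 14 days after the last quinine day. The text permits both.

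For contrast, if the same child had received AL from day 8, and 8.5.2.1 is read as covering the first course, DP/placebo could not start before day 8 + 14 = 22.

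**Step 4. Does another passage close the gap?** The prohibited list in 8.5.7.2 does not name quinine. The leaflet in Appendix VIII lists lumefantrine and quinine together, if taken within about a month, among reasons not to take the drug. The protocol sets an interval after the first and none after the second.

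**The case against.** Four arguments count against the point.

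- *The specific rule governs.* Section 8.4.3.2 names the trigger, the drug and the delay for one visit; Table 1 is a summary. Staff at that visit would probably follow 8.4.3.2. This is fair and makes the drug conflict less likely to matter in practice, but the text does not give 8.4.3.2 precedence. It also leaves the earlier unscheduled visit untouched.
- *Section 8.5.7.1 may not reach the pre-randomisation period.* It speaks of the treatment and follow-up phase, and Table 2 uses those terms for the periods after randomisation. The summary, however, counts Pre-PMC among the three follow-up phases, and Table 1 has a column for it whatever 8.5.7.1 covers.
- *The calendar reading.* It stands as an alternative and reduces the drug conflict to days 11 to 13. It does not affect the missing interval, because an unscheduled visit before day 14 is Pre-PMC on either reading.
- *The leaflet does not separate the two drugs.* That is correct. All children receive AL around discharge, and DP/placebo follows about 2 weeks later, inside the leaflet's period of about a month. The leaflet therefore does not show that quinine is the wrong choice. It shows only that spacing after either drug is a question the protocol should answer, and it answers it for one.

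A reader might also infer that an affected child has no date for randomisation. That follows only if quinine is given at the screening visit itself, against 8.4.3.2. A child treated earlier keeps the scheduled visit; what is missing is a reason to wait.

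**Conclusion.** The point holds as an inconsistency of instruction and a gap in the spacing rule. The drug conflict covers non-severe malaria in febrile, test-positive children at the screening visit: at every such visit on the phase reading, and on days 11 to 13 on the calendar reading. The missing interval is the more consequential part. It concerns children given quinine at an unscheduled visit before randomisation who meet no delay trigger.

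Three stronger inferences are not supported:

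- *That every child with malaria before randomisation is affected.* Severe malaria ends in AL, and readmission followed by AL has its own delay.
- *That the number can be gauged from the design control rate of 1,152 per 1000 child-years.* That rate counts all-cause deaths and readmissions after randomisation, so both the period and the events are wrong. The protocol gives no count, and none is assumed here.
- *That the efficacy comparison is biased, or that section 8.2.5 fails.* The treatment precedes allocation and applies to both arms alike. Section 8.2.5 argues only that no difference between arms is expected before the first study dose.

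What remains is a matter of safety and of consistency between sites. It rests on the text as written; site instructions outside the protocol may already settle it.

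**What to change.** Reconcile Table 1, 8.4.3.2, 8.5.7.1 and 8.5.2.1 so that one rule governs non-severe malaria between enrolment and randomisation, both at unscheduled visits and at the screening visit. State whether Table 1's Pre-PMC column ends at randomisation or at week 2.

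Write the delay before the first DP/placebo course so that it covers every antimalarial the reconciled rule allows and applies whether or not the child is febrile at the visit or was readmitted. Check the resulting dates against the day 11 to 28 window in Table 2.

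The choice of treatment and the length of the interval are for the sponsor's clinicians. The cost is an amendment to wording and a note to sites; sample size and analysis are unaffected.

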## 8.5. INTERVENTIONS

### *8.5.1. Standard in-hospital and post-discharge care (not study specific or study related)*

All care provided prior to and following enrolment of the patient in the study (at convalescence) will not be part of the study and will be per local (hospital) or national guideline with the exception of the full 3 day course of artemether-lumefantrine (AL) as described below. All details of non-study specific care provided by the hospital staff will be recorded in the study forms, including all drugs and dosages prescribed. The hospital teams providing care will be provided with updates of the latest national and local guidelines for in-hospital care.

*Blood transfusion and malaria treatment:* The standard in-hospital care for severe anaemia includes a blood transfusion (20mL/Kg whole blood or 10 mL/Kg Packed Red cells). In addition, patients suspected to have severe malarial anaemia also receive antimalarial treatment. In patients not able to take oral medication this consists of parenteral artesunate (2.4 mg/Kg at time 0, 12 and 24 hours), followed by a full 3 day course of artemether-lumefantrine (AL) once the patient is able to switch to oral medication. In some instances, when artesunate is not available, patients may receive parenteral quinine (10mg/kg every 8 hours) or i.m artemether. In those children who are able to take oral medication throughout, the 3-day course of AL is given without prior parenteral treatment with artesunate.

*Antibiotics* are commonly used during the in-hospital period and will be documented, but will not be part of the study intervention.

*Iron and folate supplementation* will not be part of the medication provided by the study until the time of randomisation at 2 weeks post-discharge. Until then, the use of haematinic supplementation is at the discretion of the treating clinicians. However, the hospital staff will be reminded that iron supplementation is not required during the first two weeks because the blood transfusion provided as part of the standard in-hospital care will contain adequate amounts of iron for the initial post-discharge period. See section 8.5.2.7, page 31 for details about iron supplementation during the PMC intervention period (i.e. from the first PMC dose at 2 weeks onwards).

*HIV testing*, see section 8.7.3.5, page 38.

## 8.5.2. Trial Medication and Interventions

### 8.5.2.1. PMC intervention schedule

Children will be randomised to one of the 2 treatment groups: Children in both arms will receive standard in-hospital care for severe (malarial) anaemia (blood transfusion, with or without antimalarial treatment with artesunate IV/IM). They will then all receive a 3-day course of artemether-lumefantrine (Coartem®, Novartis Pharmaceuticals) (AL) regardless of whether they were admitted with severe malarial anaemia or severe anaemia without evidence of malaria. At 2 weeks post-discharge, surviving children will be randomized to receive a standard 3-day course of DP at 2, 6, and 10 weeks post-discharge or an identical placebo regimen (Table 1, page 14). If children receive AL for malaria during any unscheduled out-patient visit or during a readmissions, the PMC schedule will be adapted accordingly such that any next course of DP is given at least 2 weeks after the start of the last course of AL; e.g. if a child was due to receive the 2nd course of DP at 6 weeks post-discharge, but is treated for malaria with AL during an unscheduled visit at 5 weeks, then the 6-week course of DP (or placebo) is provided in week 7 instead of week 6, and the subsequent course in week 11 instead of week 10.

### 8.5.2.2. Artemether-lumefantrine

The study will use the GMP formulation of Artemether-lumefantrine: Coartem®, Novartis Pharmaceuticals. Artemether-Lumefantrine will be dosed along with a small amount of food as per national guidelines. The recommended treatment is a 6-dose regimen over a 3-day period. The standard tablet or the dispersible tablets containing 20 mg of artemether and 120 mg of lumefantrine will be used and doses according to bodyweight following WHO dosing recommendations as provided in the latest WHO malaria treatment guidelines. The dose regimen will be reviewed and potentially updated if and when WHO updates their dose recommendations. The dosing is based on the number of tablets per dose according to pre-defined weight bands and the current recommendations is 5–14 kg: 1 tablet; 15–24 kg: 2 tablets; 25–34 kg: 3 tablets; and > 34 kg: 4 tablets, given twice a day for 3 days (Table 3). This extrapolates to 1.7/12 mg/kg body weight of artemether and lumefantrine, respectively, per dose, given twice a day for 3 days, with a therapeutic dose range of 1.4–4 mg/kg of artemether and 10–16 mg/kg of lumefantrine.

Table 3: Artemether Lumefantrine weight based dosing schedule

| Weight in Kg        | Number of paediatric tablets of Coartem® per dose |         |          |          |          |          |
|---------------------|---------------------------------------------------|---------|----------|----------|----------|----------|
|                     | Day 1                                             |         | Day 2    |          | Day 3    |          |
|                     | 1 st dose                              | 8 hours | 24 hours | 36 hours | 48 hours | 60 hours |
| 5 to <15  | 1                                                 | 1       | 1        | 1        | 1        | 1        |
| 15 to <25 | 2                                                 | 2       | 2        | 2        | 2        | 2        |
| 25 to ≤34    | 3                                                 | 3       | 3        | 3        | 3        | 3        |
| >34       | 4                                                 | 4       | 4        | 4        | 4        | 4        |

In some children, artemether-lumefantrine will have been provided by the hospital staff prior to enrolment into the study. This is likely in children who are severely anaemic, yet are able to take oral medication and do not require parenteral antimalarials. The number of doses and the brand of artemether-lumefantrine received prior to enrolment will be documented by the study staff on

enrolment to the study (section 8.7.3, page 38), and the subsequent number of doses of trial artemether-lumefantrine will be adjusted accordingly to ensure that the child receives a cumulative total of six doses over 3-days (section 8.7.4, page 39).

